# Efficacy of stretching exercises versus transcranial direct current stimulation (tDCS) on task performance, kinematic and electroencephalography (EEG) spectrum in subjects with slump posture: a study protocol

**DOI:** 10.1186/s13063-023-07359-0

**Published:** 2023-05-24

**Keywords:** Slump posture, Mental fatigue, Electroencephalography, Transcranial direct current stimulation, Stretching exercise

## Abstract

**Background:**

Slump sitting is a common posture in workplaces. There is limited evidence that poor posture impacts the mental state. This study aims to investigate whether slump posture results in more mental fatigue during computer typing, compared with normal posture and also to compare the effectiveness of stretching exercises with tDCS in fatigue monitoring.

**Methods:**

The sample size for this study is set at 36 participants with slump posture and 36 participants with normal posture. In the first step, to find out the differences between normal and poor posture, they will be asked to perform the typewriting task for 60 min. During the first and last 3 min of typing, mental fatigue as the primary outcome using EEG signals and further measures including kinematic behavior of neck, visual analog fatigue scale, and musculoskeletal discomfort will be assessed. Post-experiment task performance will be calculated based on typing speed and typing errors. In the next step, to compare the effect of tDCS and stretching exercises on the outcome measures, the slump posture group will receive these interventions in two separate sessions before the typing task.

**Discussion:**

With the assumption of showing significant differences in terms of outcome measures between slump and normal posture groups and also by showing the possible changes of the measures, by using either tDCS as a central modality or stretching exercises as a peripheral modality; the findings may provide evidence to indicate that poor posture has adverse effect on mental state and to introduce the effective method to overcome mental fatigue and promote work productivity.

**Trial registration:**

Registered on the Iranian Registry of Clinical Trials on 21 September 2022, IRCT Identifier: IRCT20161026030516N2.

## Administrative information

Note: the numbers in curly brackets in this protocol refer to SPIRIT checklist item numbers. The order of the items has been modified to group similar items (see http://www.equator-network.org/reporting-guidelines/spirit-2013-statement-defining-standard-protocol-items-for-clinical-trials/).

## Introduction

### Background and rationale {6a}

The employees are used to spending long periods of time in front of a computer with a dorsiflexed posture [1], in fact requiring high concentration and focus while working with a computer causes them not to pay attention to the body position. This lack of awareness of the body posture is one of the important reasons for poor posture among office workers [2].

Poor posture can change physiological, structural, physical, and functional aspects; furthermore, it can affect learning and attention [3]. For instance, slump posture decreases the rate of speaking compared to sitting upright [4] and slouched posture makes it difficult to do a math test [5]. According to Lee et al.’s study, forward head posture negatively influences the state of rest and concentration of the brain, as measured by a neuro-feedback system [6]. Based on these studies, it can be expected that poor posture causes or aggravates mental fatigue.

Mental fatigue is defined by feeling sleepy and drowsy while needing to concentrate [7] and has indicators such as feeling tired, a decrease in energy [8], mood changes [9], a decrease in performance, a decrease in accuracy and an increase in reaction time [9, 10], as well as changes in brain activity [7]. Mental fatigue has a negative impact not only on task performance in different environments, such as school [11] and workplace [12], but also on the safety of people [13]. For example; the risk of fatigue-related accidents increases, when employees get stuck in traffic after a long work day [14]. In some cases, such as those of industry workers, surgeons, drivers, and pilots, mental fatigue can lead to many hazards that cause both economic and human losses [12, 15]. Considering the high prevalence of mental fatigue in everyday modern life, it is necessary to search for efficient interventions to improve task productivity and occupational health. To date, the number of studies on tackling mental fatigue is fairly limited [16].

Exercise and physical activity have been considered as interventions for improving mental fatigue. These interventions increase the performance of the prefrontal cortex, which includes attention, memory, problem-solving, and decision-making [17]. For example, performing targeted stretching micro-breaks in surgeons without increasing the surgery time, improved their performance and concentration [18]. Furthermore, a short-term supervised exercise program including stretching exercises and joint mobility during a work shift has been shown to be more efficient than rest for reducing mental fatigue [19].tDCS is a type of non-invasive electrical stimulation that can change neural excitability in the cortex [20, 21]. tDCS can improve cognitive function in both healthy individuals and neurological patients [22, 23]. According to studies, anodal stimulation enhances learning, memory, and attention [24]. The effect of tDCS has been compared with caffeine as the most common habit to reduce fatigue. Interestingly, tDCS has a greater effect on attention and this effect also lasts longer (6 h) than caffeine (2 h) [25].

A limited number of studies have investigated the non-biomechanical part of poor posture. Most of these articles have used functional tests (such as rate of speaking) to investigate the impact of poor posture, and only one article has examined the correlation between forward head posture and brain signals as measured by a neuro-feedback system [6]; At present, there is an absence of studies utilizing QEEG to track mental fatigue in slump sitting, and in addition, the potential role of slump posture on work productivity needs to be investigated. Given the negative mental state consequences associated with poor posture and the high prevalence of slump sitting, there is a critical need to investigate changes in cortical activity and task productivity in this posture. Previous studies indicate that tDCS and stretching exercises can reduce the adverse effect of mental fatigue, however; no study has compared the effect of transcortical stimulation and stretching exercises in improving mental fatigue with neurophysiological markers of electroencephalography.

In this study, we will be trying to take a more comprehensive look at posture and assess its central aspect using brain data obtained from electroencephalography. Also, another aim of the study will be to investigate and compare the effects of transcortical stimulation and stretching exercises to reduce central complications caused by poor posture, determine the preferred intervention and introduce it for workplaces.

### Objectives {7}

The main objective of this study is to compare the mental fatigue through EEG during a prolonged typing task (i.e., 60 min) between subjects with slump and normal postures and to determine whether using tDCS or stretching exercises in the slump posture group, can deal with mental fatigue and minimize the difference in terms of mental fatigue between slump and normal posture groups.

Secondary objectives of the study include the following:To compare the kinematic parameters (i.e., entropy of neck motion and cervical angle), task performance (i.e., typing speed and errors), musculoskeletal discomfort, and visual analog fatigue scale between subjects with slump and normal postures.To compare the kinematic parameters (i.e., entropy of neck motion and cervical angle), task performance (i.e., typing speed and errors), musculoskeletal discomfort, and visual analog fatigue scale between slump posture following performing stretching exercise and normal posture.To compare the kinematic parameters (i.e., entropy of neck motion and cervical angle), task performance (i.e., typing speed and errors), musculoskeletal discomfort, and visual analog fatigue scale between slump posture following tDCS and normal postureTo compare the kinematic parameters (i.e., entropy of neck motion and cervical angle), task performance (i.e., typing speed and errors), musculoskeletal discomfort, and visual analog fatigue scale between 3 conditions of stretching exercise, tDCS, and no intervention in slump posture group.

### Trial design {8}

This is a single-center, assessor-blinded study with two parts; the first part is exploratory research with 1:1 allocation, designed to compare the outcome measures between the normal and slump posture individuals, and the second part is a crossover randomized controlled trial with a superiority design which aims to compare the effects of tDCS and stretching exercises to improve the outcome measures of the study. The study will be performed between October of 2022 and March of 2023. All the outcome measurements will be assessed during the first (T1) and last (T2) 3 min of typing. Figure 1 shows the slump posture group flowchart.

**Fig. 1 Fig1:**
[figure not shown]
Flow chart of slump posture (CVA, craniovertebral angle; TKA, thoracic kyphosis angle; tDCS, transcranial direct current stimulation; QEEG, quantitative electroencephalography; VAS, visual analog scale)

## Methods: participants, interventions, and outcomes

### Study setting {9}

The sample size is set at 36 subjects with slump posture and 36 subjects with normal posture. Participants will be recruited from TUMS (Tehran University of Medical Sciences). The present study will be conducted in the motor control laboratory at the School of Rehabilitation of TUMS. Tehran, Iran. Participants will be familiarized with the study, and they will practice with the computer. After a short break, the experiment procedures will begin.

#### Task

Previous research showed that working with a computer for a period of 45 to 60 min had reduced the performance to its minimum level [26]. So, in this study, 60 min are considered for typing, and spell-check of the word program will be turned off for all conditions. Three different Persian texts from a single book are selected for the study. The same text will be used for individuals with normal and slump posture (i.e., no intervention). But for the intervention sessions, the text will be changed to prevent the learning effect.

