## Interventions

### Explanation for the choice of comparators {6b}

The normal posture group will participate just once while the slump posture group will carry out the experiment in 3 separate sessions (i.e., no intervention, stretching exercise, and tDCS) with a week interval between sessions. The sequence of sessions will be randomized. The assessor involved in analyses will be blind to groups and conditions.

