### Outcomes {12}

#### Task performance

Task performance will be obtained by typing speed (i.e., characters per minute) and typing errors (i.e., errors per minute), which will be calculated by the assessor at the end of the tests.

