## Assignment of interventions: allocation

### Sequence generation {16a}

Randomization sequence will be generated using a web-based randomization service (https://statpages.info/latinsq.html). Given three states for slump posture group (i.e., no intervention, tDCS, and stretching exercise), there will be six different possible orders (ABC, ACB, BAC, BCA, CAB, and CBA). Each order will be performed five times in an equal ratio.

Randomization will be done at TUMS. Access to the randomization schedule will be restricted to an investigator who is not involved in the recruiting process.

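### The typing text is tied to the condition, so text difficulty cannot be separated from any intervention-versus-none or intervention-versus-normal difference

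*Protocol article*

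**What the plan says.** The Task section (under Study setting {9}) fixes the material to be typed: "Three different Persian texts from a single book are selected for the study". It then allocates the texts by condition. For the normal group and the untreated slump session, "The same text will be used for individuals with normal and slump posture (i.e., no intervention"). For the other two sessions, "But for the intervention sessions, the text will be changed to prevent the learning effect".

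Randomisation concerns something else. Sequence generation {16a} covers the order of the three conditions: "there will be six different possible orders (ABC, ACB, BAC, BCA, CAB, and CBA"), and "Each order will be performed five times in an equal ratio". Nothing in the article rotates texts over conditions or sessions. On the number of visits, item {6b} on comparators states: "The normal posture group will participate just once while the slump posture group will carry out the experiment in 3 separate sessions".

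Task performance is measured as "typing speed (i.e., characters per minute) and typing errors (i.e., errors per minute"). Objectives {7} plans comparisons of stretching with normal, tDCS with normal, and the three slump conditions with one another. Statistical methods {20a} names MANOVA between groups and repeated measures ANOVA with LSD tests within the slump group, with no term for text.

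**The concern.** The stated purpose of changing the text is to avoid a learning effect. That purpose only requires that nobody types the same text twice. It does not require that the untreated session always has one particular text and the treated sessions always have others.

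Under the stated rule, a participant's treated and untreated sessions differ in two respects at once: the intervention and the text. Randomising session order balances practice and time effects over conditions. It does not balance text, because the text moves with the condition whatever the order. If one text has harder vocabulary or heavier punctuation, the difference in speed or errors will be read as an effect of stretching or tDCS. It could equally hide a real one.

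At stake are each intervention against no intervention in the second part, and the objectives that ask whether an intervention closes the gap to normal posture. The slump (no intervention) versus normal comparison uses a common text and is sound in this respect.

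**Working it through.** The protocol has no figure of its own to reproduce here. The question is first one of estimability, then of size.

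**Step 1: which contrasts can be separated from text?** Take 36 slump participants with three sessions each and the six condition orders equally represented. The model is

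outcome = participant + session + condition + text.

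It has 36 + 2 + 2 + 2 = 42 columns. A contrast is estimable if adding it as a row to the design matrix leaves the rank unchanged. The Task section does not say how the second and third texts are divided between tDCS and stretching, so both possibilities were checked, along with full crossing.

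| Text scheme | Rank (of 42) | tDCS − none | Stretching − none | tDCS − stretching |
|---|---|---|---|---|
| Each condition has its own text | 40 | no | no | no |
| Text 1 for no intervention; texts 2 and 3 rotated over the interventions | 41 | no | no | yes |
| All three texts crossed with condition | 42 | yes | yes | yes |

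Both intervention-versus-none contrasts are inestimable apart from text however the remaining texts are split. The same holds for slump-after-intervention versus normal, because the normal group types only the first text. Whether tDCS versus stretching is also affected depends on the unstated split.

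**Step 2: how large could the distortion be?** The documents give no text effect, so the following is an assumption shown over a range. Let d be the text shift in SDs of the within-person difference, with no true intervention effect. The two-sided paired t-test at 0.05 then has noncentrality d√n on n − 1 degrees of freedom, and the rejection probability follows from the noncentral t distribution. The values of n are those in Sample size {14}: 30 needed for the second part, 36 after the dropout allowance. For example, with d = 0.3 and n = 30, the noncentrality is 0.3 × √30 = 1.64 against a critical value of 2.045, which gives 0.355.

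| d | n = 30 | n = 36 |
|---|---|---|
| 0 | 0.050 | 0.050 |
| 0.1 | 0.083 | 0.090 |
| 0.2 | 0.185 | 0.215 |
| 0.3 | 0.355 | 0.417 |
| 0.4 | 0.563 | 0.646 |
| 0.5 | 0.754 | 0.831 |

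For slump-after-intervention versus normal with 36 per group, the noncentrality is d√(36/2) on 70 degrees of freedom, with d now in between-person SDs. Shifts of 0.2, 0.3 and 0.5 give 0.133, 0.241 and 0.553.

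**Step 3: does crossing fit the planned numbers?** Three texts have six orders. Six condition orders × six text orders = 36 combinations, one per planned slump participant. Enumeration gives 36 × 3 = 108 sessions, with each of the nine condition-by-text cells and each of the nine session-by-text cells filled 12 times.

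**The case against.** The strongest reply is that inseparable does not mean biased. The texts come from one book, speed is counted in characters (which partly offsets word length), and an hour of typing averages out local difficulty. All this makes a large text effect less likely. It does not establish equal difficulty, and the article reports no matching or pretest. The rejection rates above rest on an assumed shift; at 0.1 SD the inflation is modest.

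A second reply is that the primary outcome is EEG mental fatigue, recorded in the first and last three minutes of typing, and a constant text offset would cancel in a within-session change. That is true and limits the reach of the point for EEG and for the other measures taken at both times. It does not remove it. A text that tires people faster would still show in the change, and Statistical methods {20a} does not name a change-score analysis. Speed and errors are calculated at the end of the tests, so this protection does not clearly apply to them.

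Third, Trial design {8} describes the second part as comparing tDCS with stretching, and that contrast survives if the second and third texts are rotated between them. This stands as a possibility, but the article does not say that they are.

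Fourth, dropout would disturb an exact 36-cell balance, and using three texts in the normal group adds some between-text variance to the first part. Both are fair; a text term in the model deals with moderate imbalance and absorbs the between-text variance.

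Finally, Trial status expected recruitment to finish in February 2023, so redesign may no longer be possible. That changes which remedy applies, not whether the confounding exists.

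**Conclusion.** The concern holds. By a stated rule of the protocol, text is completely aliased with intervention versus no intervention and with slump-after-intervention versus normal, and no later analysis can undo this. The conclusion follows from the design alone and needs no assumption about difficulty.

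The size of any bias is unknown. If the texts differ by 0.3 to 0.5 SD of the paired difference, false-positive rates run from 36% to 83% over the two sample sizes; at 0.2 SD they are 19% to 21%, and at 0.1 SD 8% to 9%. These figures assume a two-sided paired test at 0.05 and no true effect. Exposure is most direct for typing speed and errors. It is weaker for EEG, the fatigue and discomfort scales and kinematics if within-session change is analysed. The point must be fixed, because it decides whether central planned contrasts can be interpreted at all.

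**What to change.** If sessions remain to be run:

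- Cross text order with condition order, so that each of the 36 slump participants receives one of the 36 combinations. Nobody retypes a text, so the protection against learning is kept. The session list must then cover 36 participants; the current six orders × five covers 30.
- Give each text to 12 normal-posture participants. Each text is then typed by 12 slump participants in every condition and by 12 normal participants, so the group comparisons stay text-matched.
- Add text as a fixed factor, alongside session, in the analysis of the three conditions, and add text to the group comparisons.

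The cost is a revised session list and one model factor with 2 degrees of freedom. No extra participants, sessions or texts are needed.

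If sessions were completed under the stated rule, report how the second and third texts were assigned, give any evidence that the three texts are equally difficult, and state that intervention-versus-none and intervention-versus-normal differences in typing outcomes cannot be separated from text. The same caution, in weaker form, should accompany the EEG and other outcomes.

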### Eligibility criteria {10}

Subjects will be included, if they meet the following criteria: age between 22 and 40 years, have a BSc degree, fluency in Persian, prior experience with computer typing and lack of 10-finger typing skills, no history of shoulder and spine surgery or fracture, no obvious scoliosis, body mass index (BMI) < 30. Postural angles including the craniovertebral angle (CVA) and the thoracic kyphosis angle (TKA) are considered as follows: CVA ≥ 50 and TKA between 20 and 40 for the normal posture group, CVA < 50 and TKA > 40 for the slump posture group. In addition, cardiac or metabolic diseases, severe head injury, metals in the head, psychological problems, seizures, a history of taking medications that affect the central nervous system, and pregnant women will not be included in the study.

The typewriting background will be controlled by a self-report of daily amount of computer usage and years of computer use. There will be no significant difference between the two groups with respect to computer usage.

Before the tests, subjects are asked to follow these: (1) proper and adequate sleep, (2) avoid using drugs or alcohol in the last prior week, and coffee in the last prior 8 h.

Excluding criteria: those individuals who will not be interested in continuing the study for any reason.

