#### Kinematic parameters

Kinematic properties including the non-linear dynamical features of neck motion and cervical angle changes will be measured. For this, markers will be placed on the tragus, spinous process of C7, and corner of the eye. A SAMSUNG (A50, South Korea) camera (30 frames per second) will be placed at a distance of 2.18 m from the participant and a height of 1.25 m [42]. In the first and last three minutes of typing, a recording will be taken. Then the recording will be imported to Kinovea software version 0.8.15.

Mean and standard deviations of CVAs will be used to assess the cervical angle changes, and Sample Entropy will be calculated for neck motion Entropy. Entropy Analysis will be calculated in Excel software using SEN = -ΣPi ln Pi formula for each marker, where Pi is the spectral amplitudes of path bin i, Σ Pi = 1, and ln = denotes the natural logarithm.

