## Statistical methods

### Statistical methods for primary and secondary outcomes {20a}

Data analysis will be performed using SPSS, version 22 (IBM, NY, USA). Baseline characteristics such as age, weight, height, BMI, years of computer use, and daily computer usage will be summarized with standard descriptive statistics. Depended variables will be described with means and standard deviations. The normality of distribution will be checked by Kolmogorov–Smirnov.

Multivariate ANOVA (MANOVA) will be used to compare the variables between correct and slump posture groups.

Statistical analysis of the outcomes of 3 conditions in the slump posture group will be conducted using repeated measures ANOVA and LSD (least significant difference) post hoc test. The significance level of tests will be considered at 0.05. Mean difference and standardized mean difference and their 95% confidence intervals (Cohen’s D) will be calculated as effect sizes.

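### Part 1 states no adjustment for residual confounding between the posture groups, and mean CVA during typing is a between-group outcome although CVA forms the groups

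*Protocol article*

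**What the plan says.** The Trial design section describes Part 1 thus: "the first part is exploratory research with 1:1 allocation, designed to compare the outcome measures between the normal and slump posture individuals". Despite the mention of allocation, posture is not assigned. Eligibility criteria {10} sorts participants by measured angles: "CVA ≥ 50 and TKA between 20 and 40 for the normal posture group, CVA < 50 and TKA > 40 for the slump posture".

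The same section limits both groups on age, education, typing skill, BMI and health. It says typing background will be controlled through self-reported computer use, and continues: "There will be no significant difference between the two groups with respect to computer usage". It names no matching, stratification or adjustment.

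Statistical methods {20a} gives one analysis for this comparison: "Multivariate ANOVA (MANOVA) will be used to compare the variables between correct and slump posture groups". It names no covariate and does not list the variables. On baseline data it says: "Baseline characteristics such as age, weight, height, BMI, years of computer use, and daily computer usage will be summarized with standard descriptive statistics".

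The first secondary objective, for slump versus normal posture, begins: "To compare the kinematic parameters (i.e., entropy of neck motion and cervical angle), task performance". Under Kinematic parameters, the angle is taken from video of the first and last three minutes of typing: "Mean and standard deviations of CVAs will be used to assess the cervical angle changes".

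**The concern.** There are two separate issues.

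The first is confounding. The Abstract hopes to provide evidence that poor posture adversely affects mental state, and this comparison is part of the main objective. In a non-randomised comparison, differences between the groups in computer use, or in age and BMI within the permitted limits, could contribute to a difference in EEG or typing performance. The protocol recognises computer use as something to control, but what it offers is a predicted test result. A non-significant test in a small sample says little about balance.

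The second is circularity. CVA below 50 versus 50 or above is a grouping criterion, and mean CVA during typing is then compared between the same groups. A difference there largely reflects how the groups were formed. If the variable also sits in the MANOVA, a significant omnibus test could arise with no difference in EEG, the primary outcome.

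**Working it through.** The protocol gives no figure on this point to reproduce. From it come 36 per group, alpha 0.05 and the CVA cut at 50. Imbalance sizes, correlations and the CVA distribution are not given; they are assumptions, shown as ranges.

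**1. What a non-significant balance test shows.** Two-sided t-test, n = 36 per group, 70 df, critical value 1.994, noncentrality = d × √(n/2) = d × √18.
- d = 0.4: noncentrality 1.70, power 38.8%, so missed 61%.
- d = 0.5: noncentrality 2.12, power 55.3%, so missed 45%.

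**2. Effect on type I error.** Suppose posture has no effect, a covariate differs by e SD, and it correlates r with the outcome. The unadjusted group difference is then biased by about e × r SD. Two-sided rejection rates at 36 per group, both tails counted:

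| e | r | Bias (SD) | Rejection |
|---|---|---|---|
| 0.3 | 0.3 | 0.09 | 6.6% |
| 0.4 | 0.4 | 0.16 | 10.3% |
| 0.5 | 0.5 | 0.25 | 18.2% |

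**3. CVA difference from selection alone.** Assume screening CVA is normal and correlates r with mean CVA during typing; selection on kyphosis is ignored. With a population mean of 50, the halves above and below the cut lie 2 × 0.798 = 1.596 SD apart, and the variance of screening CVA within each half is 0.363 of the total. Hence d = 1.596r / √(1 − 0.637r²).
- r = 0.3: 0.479 / √0.943 = 0.49
- r = 0.5: 0.798 / √0.841 = 0.87
- r = 0.7: 1.117 / √0.688 = 1.35

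Varying the mean over 48 to 52 and the SD over 4 to 6 gives 0.49–0.51, 0.87–0.90 and 1.35–1.39. A t-test on CVA at 36 per group is then significant about 54–57%, 95–96% and more than 99% of the time.

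**4. Effect on an omnibus test.** Two-group MANOVA (Hotelling T²) with p uncorrelated outcomes of which only mean CVA differs. The F test has p and 72 − p − 1 df and noncentrality (n/2)d² = 18d². Rejection rates:

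| CVA d | 18d² | p = 5 | p = 8 | p = 12 |
|---|---|---|---|---|
| 0.5 | 4.5 | 30% | 24% | 19% |
| 0.87 | 13.6 | 79% | 69% | 58% |
| 1.0 | 18.0 | 90% | 83% | 73% |

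The number of outcomes is also an assumption, because the protocol does not list them.

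**The case against.** Several points on the other side are fair.

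- A reader might infer that confounding is uncontrolled. It is not: both groups share the eligibility limits, type the same text and are tested before noon. Nothing in the protocol shows that slump participants are older, heavier or heavier computer users. What stands is that residual confounding is not addressed.
- The sentence on computer usage may be a compressed commitment to recruit comparable groups, and a covariate list is often left to an analysis plan. The statement of no additional analyses falls under the item on subgroup-type analyses, so it need not bar covariates in the main model. Even so, the sentence promises a test result and names no means of achieving it.
- A reader might infer that the CVA difference is guaranteed by construction. Grouping uses a baseline photograph and the outcome comes from video during typing, another time and task. At r = 0.2, d is only about 0.33 and the CVA test is significant about 28% of the time. The point is one of likelihood. It concerns the mean level only, not variability or change from T1 to T2.
- That mean CVA enters the MANOVA is inferred from the objectives together with an unlisted set of variables. It is the natural reading, since no other method is given for this comparison, but it is not explicit.
- Part 1 is labelled exploratory, and nowhere does the protocol say that a significant omnibus test counts as evidence on mental state. A CVA-driven result misleads only if it is read without the EEG result. This limits the harm without removing the cause.

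**Conclusion.** The point holds in a limited form. The comparison is observational, its only stated analysis has no covariate, and promised non-significance is neither a method of control nor evidence of balance. Under the assumed imbalances and correlations, type I error rises from 5% to between about 7% and 18%.

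Mean CVA during typing is better treated as a check on the grouping than as a tested Part 1 outcome. How far it could drive an omnibus test depends strongly on the unknown screening-to-typing correlation: rejection with no EEG difference runs from about 19–30% at d = 0.5 to 73–90% at d = 1.0, if mean CVA is in the model. The protocol does not support saying that confounding is wholly uncontrolled, that the CVA difference is certain, or that a false conclusion on EEG must follow.

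**What to change.** 1. Add age, BMI, years of computer use and daily computer use as prespecified covariates in the Part 1 model, for example as a MANCOVA. Replace the sentence promising no significant difference in computer usage with a statement of this adjustment.
2. Take mean CVA level out of the slump-versus-normal tests and report it descriptively as a posture check. Keep its change from T1 to T2 and its variability as tested outcomes, and keep CVA as an outcome in the slump crossover.

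Replacing the MANOVA by a separate model for each outcome is not needed to cure this; it is a matter of preference and would raise its own multiplicity question.

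The cost is about four degrees of freedom and one fewer tested between-group outcome. The covariates are already to be collected. Adjustment reduces bias from these four variables only, so the comparison remains observational.
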